## Abstract

**Background:**

Childhood anxiety presents a serious mental health problem, and it is one of the most common forms of psychological distress reported by youth worldwide. The prevalence of anxiety symptoms amongst South African youth is reported to be significantly higher than in other parts of the world. These high prevalence rates become even more significant when viewed in terms of children with visual impairments, as it is suggested that children with physical disabilities may be more prone, than their non-disabled peers, for the development of psychological difficulties.

**Objectives:**

The main aim of this study is to develop, implement and evaluate a specifically tailored anxiety intervention programme for use with South African children with visual impairments.

**Method:**

A specifically tailored cognitive-behavioural therapy-based anxiety intervention, for 9–13 year old South African children with visual impairments, will be evaluated in two special schools. The study will employ a randomised wait-list control group design with pre- post- and follow-up intervention measures, with two groups each receiving a 10 session anxiety intervention programme. The main outcome measure relates to the participants’ symptoms of anxiety as indicated on the Revised Child Anxiety and Depression Scale.

**Conclusion:**

If the anxiety intervention programme is found to be effective in reducing symptoms of anxiety, this universal intervention will lay down the foundation upon which future contextually sensitive (South African) anxiety intervention programmes can be built.

## Introduction

A substantial body of literature indicating that childhood anxiety presents a serious mental health problem has now been amassed (Barrett & Turner 2001). Firstly, the literature indicates that anxiety is one of the most common forms of psychological distress reported by youth (Barrett & Sonderegger 2005; Dadds *et al.*
1997). A recent meta analytic prevalence study indicated that an average of 12.3% of school-aged children (ages 6–12) experience significant symptoms of anxiety (e.g., Costello *et al.*
2011, 2003; Heiervang *et al.*
2007; McArdle, Prosser & Kolvin 2004; Mullick & Goodman 2005; Petersen *et al.*
2006). Secondly, although experiencing transient fears and anxieties is deemed to be a normal part of development for most children; for some these experiences may intensify and persist over time, causing interferences in daily functioning (Barrett, Lock & Farrell 2005; Silverman 2011). Thirdly, the experience of childhood anxiety has been associated with a number of somatic difficulties such as fatigue, restlessness, irritability, and sleep disturbances (Beidel, Christ & Long 1991; Pina & Silverman 2004) and psychosocial impairments such as problems with peer relations, low self-esteem, immaturity, impaired academic functioning, and concentration problems (Cooley, Boyd & Gratos 2004; Farrell & Barrett 2007; Messer & Beidel 1994; Motoca, Williams & Silverman 2012). Fourthly, if left untreated, severe symptoms of anxiety can take on a chronic and unremitting course (Barrett & Turner 2004; Cole *et al.*
1998; Weems & Silverman 2013), and many adults who are diagnosed with an anxiety disorder can trace the onset of symptoms back to their childhood (Rapee & Barlow 1993). Given this suggested relationship between childhood anxiety and adult psychopathology, it is essential for symptoms of anxiety to be addressed as early as possible (Cobham 2003), and promising in this regard is the increased evidence pointing to the amenability of childhood anxiety symptoms to brief psychosocial interventions (Lowry-Webster, Barrett & Dadds 2001; Silverman, Pina & Viswesvaran 2008).

Yet, despite these promising results, research indicates that less than 20% of children who require treatment for anxiety will receive clinical intervention (Day & Roberts 1991; Olfsen *et al.*
2003), and of those who do, a large number will terminate prematurely (Kazden 1996; Pina *et al.*
2003), fail to respond (Donovan & Spence 2000; Rey, Marin & Silverman 2011) or, despite treatment, continue to experience recurrent difficulties (Last *et al.*
1996).

In addition, long waiting lists, high costs, high instances of family drop outs, and no show rates also influence access to treatment (Weist 1999). As a result, health policies across the world increasingly promote prevention as the most important direction in which mental health services should move (Barrett & Turner 2004; Lowry-Webster, Barrett & Lock 2003). Prevention offers a positive adjunct to treatment, as prevention programmes can reach a large number of individuals over a shorter period of time; avoid high levels of personal distress for children and their families; and offer a cost-effective and efficient means of intervention prior to the onset of psychopathology (Farrell & Barrett 2007).

The South African prevalence rates of anxiety symptoms are even higher than the above-mentioned international estimates suggest, with Muris and his colleagues (Muris *et al.*
2002) reporting prevalence rates of anxiety symptomology between 22% – 25.6% in children aged 7 to 13 years. These findings were confirmed in subsequent South African studies (Burkhardt, Loxton & Muris 2003; Muris *et al.*
2006). Mostert and Loxton (2008) noted these high prevalence rates and identified the need for a suitable anxiety intervention programme which could be implemented within the South African context. Previous international studies and also the World Health Organization (WHO 2004) had identified Barrett’s (2004) cognitive behavioural therapy (CBT) based FRIENDS Programme to be an efficacious intervention for the reduction of anxiety symptoms in youth (see Briesch, Hagermoser Sanetti & Briesch [2010] for an overview). As a result, Mostert and Loxton (2008) conducted a pilot study to explore the effectiveness and suitability of the FRIENDS Programme for use with South African children. This study reported promising results and its outcomes were in line with the government's white paper on the transformation of the South African health care system, as the study promoted prevention as an important strategy for the enhancement of the mental and physical health of the nation (DOH 1997).

The above-mentioned anxiety factors, their high prevalence rates, and identified need for a suitable intervention programme, become even more significant when viewed in terms of the population of children with visual impairments, who are often marginalised, as previous research involving children with physical disabilities suggests that they are at increased risk of developing psychological difficulties when compared to their non-disabled peers (see Gullone [1996] for an overview). Despite this identified risk, this population has been neglected in previous fear and anxiety research. The last international study to touch on this topic was conducted by Weimer and Kratochwill more than two decades ago (1991) in Wisconsin (USA).

Identifying this gap in the literature, the authors (Visagie *et al.*
2013) conducted an exploratory (baseline) study with South African children with visual impairments. Results indicated that the overall fear profiles of children with visual impairments, and children with normal sight, did not differ significantly (Visagie *et al.*
2013). This similarity indicates that the two populations (children with and children without visual impairments) have similar needs. As the need for a suitable anxiety intervention programme was highlighted in the general South African population (children without visual impairments) (Burkhardt *et al.*
2003; Mostert & Loxton 2008; Muris *et al.*
2006), the same can be said for this specific group. Children with visual impairments also require a suitable and accessible anxiety intervention programme (Loxton, Visagie & Ollendick 2012; Visagie *et al.*
2013).

On closer evaluation of the study by Visagie *et al.* (2013), the need for a suitable anxiety intervention programme was noted to be especially prominent for a specific sub-group of children with visual impairments (i.e. children with severe visual impairment). In their 2012 paper Loxton, Visagie and Ollendick (2012) highlighted significant differences in fearfulness between three groups of visually impaired children who had varying levels of sight (i.e. partially sighted, severely visually impaired and totally blind). These levels of vision can be viewed on a sliding scale (i.e. children who are partially sighted have the most vision; children with severe visual impairment have less vision, but they are not totally blind; and the totally blind children have no level of measureable vision). Children with severe visual impairment (i.e. children who have a degree of light perception and movement detection, but who cannot function optimally without assistance and cannot read print material (WHO 2000), were more fearful than the partially sighted and totally blind children. This group reported the highest number (M = 42.09, SD = 17.84) and also level (M = 171.63, SD = 28.60) of fear. This reported number of fears is almost double the number reported by the children with normal sight (M = 24.66, SD = 13.12). The level of fear in children with normal sight was also lower (M = 146.15, SD = 25.33).

Thus, children with severe visual impairment can be identified as a high-risk sub-group within the broader population of children with visual impairments, for the possible development of later anxiety disorders. A possible suggestion for this sub-group's greater instance of fearfulness could relate to the fact that the visual difficulties, of this group of children, are the most differentiated and difficult to understand. The totally blind children can see nothing; therefore, they need assistance in most unfamiliar situations. On the other hand, partially sighted children usually have enough sight to help themselves and move around independently, and the children with severe visual impairment are in the middle, this group's visual difficulties may be the most complex and most disabling.

Although children with severe visual impairments have a degree of measurable vision, they may find it difficult to function independently in an unfamiliar environment. Therefore, the uncertainty when they are faced with new situations and possibilities may contribute directly to their higher fear reactivity (Bensch 2010; Loxton *et al.*
2012; Sacks *et al.*
2006; Visagie *et al.*
2013). Therefore, it is essential for these children to have access to suitable intervention programmes focused on the development of appropriate coping strategies and problem solving skills to enable them to deal competently with anxiety symptoms when they arise.

Although Mostert and Loxton (2008) obtained favourable outcomes with the FRIENDS Programme with a group of South African children, their study did incur some limitations. It was noted that the FRIENDS acronym (F for feeling worried?, R for Relax and feel good, I for Inner thoughts, E for Explore plans of action, N for Nice work, reward yourself!, D for Do not forget to practise, and lastly S for Stay cool and calm! (Barrett 2004, cited in Mostert 2007), which is aimed to aid children in remembering the coping steps to take when faced with a problem, was difficult for some South African children to remember and problematic to translate into Afrikaans (Mostert & Loxton 2008). Furthermore, Mostert and Loxton (2008) concluded that although the FRIENDS Programme has been used successfully in other countries, South African socio-contextual issues (the high incidence of crime and poverty) should not be ignored – research should in addition be focused on constructing a socially relevant anxiety intervention programme that considers the impact of these factors (Mostert & Loxton 2008). In addition, the FRIENDS Programme is not suitable for use with children with visual impairments, as its content (i.e. cartoons, colouring-in pictures, workbook and visual-based activities) is not very accessible to this specific population.

To summarise, the following six factors motivated the proposed study:
The high prevalence rates of anxiety symptomology in the general population (especially in South Africa)The suggestion that visually impaired children are at increased risk for the development of anxiety disorders when compared to their sighted counterpartsThe lack of anxiety research involving children with visual impairmentsThe unique South African socio-cultural contextThe benefits associated with prevention and early intervention with regards to childhood anxietyThe inaccessibility and appropriateness of existing anxiety intervention programmes.

As a result, the proposed study will aim to develop, implement and evaluate an anxiety prevention or early intervention programme (from here on referred to as an anxiety intervention programme), which is specifically tailored to meet the needs of children with visual impairments within the South African context. As far as the researchers can ascertain, no studies focussed on anxiety prevention and early intervention programmes, for children with visual impairments, have been conducted previously.

Thus, the primary aim of the study is to develop, implement and evaluate a specifically tailored anxiety intervention programme for use with South African children with visual impairments. This aim will unfold in the following three steps:

develop an accessible anxiety intervention programme which can be used with South African children with visual impairments (programme development phase).implement this anxiety intervention programme successfully (programme implementation phase).evaluate the effectiveness of this anxiety intervention programme in maintaining emotional health (i.e. preventing an increase in symptoms of anxiety as measured on the Revised Child Anxiety and Depression Scale [RCADS] [Chorpita *et al.*
2000] [programme evaluation phase]).

Specifically, it is expected that firstly, there will be a significant reduction in anxiety scores on the RCADS from Time 1 (T1) to Time 2 (T2) for the immediate intervention group (IIG), and secondly, there will be a significant reduction in anxiety scores on the RCADS from T2 to T3 for the delayed intervention group (DIG).

## Method

A specifically tailored CBT-based anxiety intervention for South African children with visual impairments will be evaluated in two special schools that cater for children with visual impairments. This study is set up as a randomised wait-list control group design with pre-, post-and follow-up intervention measures, with 60 participants randomly assigned to an IIG (*n* = 30) and a DIG (*n* = 30). Before implementation of the programme 10 participants from each group will be randomly selected to take part in a focus group. The focus group will be aimed at obtaining the participants’ personal inputs and to pilot certain sections of the programme before final implementation. Both of the programme's groups will receive the 10 session anxiety intervention programme**.** The participants will complete baseline (T1), post intervention (T2 for IIG and T3 for DIG) and 3 month (T3 for IIG and T4 for DIG) or 6 month (T4 only for IIG) follow-up assessments.

The research design can be represented as follows:

R  IIG T1   X  IIG T2     IIG T3  IIG T4

R  DIG T1     DIG T2  X  DIG T3   DIG T4

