## Programme evaluation

As mentioned above, all assenting children from School 1 and School 2 will randomly be assigned to 1 of 2 groups at their respective school (an IIG or a DIG). The IIG groups from School 1 and School 2 will be combined to form one large IIG, whilst the DIG groups from School 1 and School 2 will be combined to form one large DIG.

The evaluation phase will comprise both a quantitative and qualitative component (more information about the qualitative component is given below). For the quantitative evaluation, all assenting children in the IIG and DIG (approximately 60 participants) will be administered a short biographical questionnaire (only at T1) and three self-report questionnaires at pre (T1), post (T2), and follow-up (T3 and T4) intervention. Children in the IIG will receive the intervention programme before the children in the DIG. It is envisaged that the programme will be delivered to the two groups (the IIG and DIG) of children according to the following outline:

Initial assessment of all children, IIG and DIG (T1)Children in the IIG receive the anxiety intervention programme (5 weeks)Re-assessment of all children, IIG and DIG (T2)Children in the DIG receive the anxiety intervention programme (5 weeks)Re-assessment of all children, IIG and DIG (T3)Final assessment of all children, IIG and DIG (T4 – It will be 6 months after the children in the IIG received the intervention and 3 months after the children in the DIG received the intervention). Resulting from time constraints, where all assessments should be conducted within one academic year, there will be no 6 month follow-up for the DIG, and no wait period for the IIG.

It will be possible to measure:

The stability of the measures when untreated over time (The DIG will act as a wait-list control group using T1 and T2 comparisons)The impact of the anxiety intervention programme immediately after completion (using immediate pre and post-data from both groups – IIG [T1 and T2]; and DIG [T2 and T3])The maintenance of the effects of the anxiety intervention programme over time following intervention (IIG using T2, T3 [3 month] and T4 [6 month] comparisons, and DIG using T3 and T4 [3 month] comparisons)

The following six hypotheses are to be tested during the evaluation phase of the proposed study (four hypotheses pertain to between group effects and two hypotheses pertain to within group effects).

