## Data collection

Questionnaires will be made available in four different input modes relating to the individual participant's specific needs and degree of visual impairment. In some cases the original print versions of the questionnaires will be provided and read by means of a magnifying aid, questionnaires will also be put in a large print format (A3), and for those participants who cannot read print, the questionnaires will be made available in braille or in an audio format. The modes of response will also be adapted to suit the individual participant's communication needs. Participants who are able to read the standard or large print copies of the questionnaires can indicate their answers in the spaces provided, and for the participants using braille or recorded versions of the questionnaires, specially prepared answer sheets will be made available.

In previous studies (King, Gullone & Stafford 1990; Matson *et al.*
1986; Ollendick, Matson & Helsel 1985; Wilhelm 1989) where the fears and anxieties of visually impaired children were assessed using self-report measures (e.g. The Revised Fear Survey Schedule for Children, FSSC-R; The South African Fear Survey Schedule for Children, FSSC-SA; and the Revised Children's Manifest Anxiety Scale, RCMAS) similar adaptations were made with great success. Children will complete the questionnaires at their school with the help of the research facilitators. Guidelines put forth by Visagie and Loxton (2014) about the child-friendly assessment and the accomodations needed for children with visual impairments to complete self-report surveys, will be implemented and followed throughout the process of data collection.

The questionnaires will be administered to all participants (IIG and DIG) on four occasions:

Immediately before delivering the anxiety intervention programme to the IIG (T1) (Baseline)Immediately after delivering the anxiety intervention programme to the IIG, and before delivering the anxiety intervention programme to the DIG (T2)Immediately after delivering the anxiety intervention programme to the DIG (T3)At follow-up, six months after delivering the programme to the IIG, and three months after delivering the programme to the DIG (T4)

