### Statistical analyses

The Statistical Package for the Social Sciences (SPSS) (Van Leeuwen *et al.*
2006) will be used to calculate descriptive and non-parametric statistics. As a result of the envisaged small sample size (*N* = 60), a Mann-Whitney test will be used to determine the significance of differences between the quantitative pre-and-post intervention measures (George & Mallery 2006). Pre-intervention (T1) scores will be analysed to determine the equivalence of the IIG and the DIG, before the intervention and change scores (difference between the pre-and post-intervention scores) for the IIG and DIG will be compared to evaluate change as a result of the intervention programme. Qualitative data will be analysed by means of thematic content analyses.

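### Ten of the 30 wait-list children pilot parts of the programme after randomisation, yet the plan uses the whole arm as untreated from T1 to T2

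*Protocol article*

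**What the plan says.** The Method section of the protocol article describes "60 participants randomly assigned to an IIG (*n* = 30) and a DIG (*n* = 30"). The next sentence reads: "Before implementation of the programme 10 participants from each group will be randomly selected to take part in a focus group". The focus group collects the children's views, and it also serves "to pilot certain sections of the programme before final implementation". The phrase about each group presupposes that the arms already exist.

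The design diagram in the same section places R before T1 in both rows. The outline under Programme evaluation opens with a T1 assessment of IIG and DIG children, so allocation precedes T1 there too. Data collection times T1 as "Immediately before delivering the anxiety intervention programme to the IIG (T1").

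Programme evaluation lists, among the things the design can measure: "The stability of the measures when untreated over time (The DIG will act as a wait-list control group using T1 and T2 comparisons"). All of the roughly 60 children are assessed. Under Statistical analyses, "change scores (difference between the pre-and post-intervention scores) for the IIG and DIG will be compared". The article describes no exclusion, replacement or separate handling of the 20 focus-group children.

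**The concern.** T1 to T2 is the only interval in which one arm has the programme and the other does not, because the DIG starts straight after the IIG finishes. The second between-group hypothesis and the change-score comparison both depend on it. If a third of the comparator arm has already worked through sections of the programme, the description of that arm as untreated is not accurate for those children, and the contrast may understate the programme's effect.

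A second, smaller point comes from the same sequence. T1 is a self-report score taken after allocation and possibly after piloting. It is therefore not secured as a baseline that precedes both allocation and exposure, and a change score carries any distortion of the baseline into the effect.

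**Working it through.** **Inputs from the article.** 30 + 30 = 60 children, which agrees with the stated total. 10 per arm enter the focus group: 10/30 = 33.3% of the DIG, and 20/60 = 33.3% overall. The analysis compares change scores between arms with a Mann-Whitney test.

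**Assumptions (none is in the article).**
- c: the share of the full programme effect that the piloted sections deliver, from 0 to 1.
- d: the full effect in standard deviations of the change score. I use 0.5 and 0.8 for illustration.
- Two-sided alpha of 0.05.

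**Step 1: does the order of pilot and T1 matter for the size of the loss?** Suppose the pilot effect lasts to T2 and overlaps with the programme, so that a piloted IIG child ends at d and no further.

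- Pilot after T1: piloted DIG children improve by c·d between T1 and T2, so the DIG mean improves by c·d/3. The IIG mean improves by d. Contrast: d − c·d/3 = d(1 − c/3).
- Pilot before T1: piloted DIG children show no further change. Piloted IIG children have only (1 − c)d left to gain, so the IIG mean improves by (20·d + 10·(1 − c)d)/30 = d(1 − c/3). The contrast is the same.

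The order does not matter because the draw is balanced: any pilot effect at T1 is the same in both arms on average.

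**Step 2: when is there no loss?**
- The pilot has no effect: c = 0.
- The pilot effect has gone by T2: piloted DIG children then end where unpiloted ones do, and the contrast is d.
- The pilot simply adds to the programme. With a pilot before T1, piloted IIG children still gain the full d and DIG children gain nothing. With a pilot after T1, both arms gain an extra c·d/3, which cancels. The contrast is d either way.

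**Step 3: size under overlap.** Sample inflation for equal power is 1/(1 − c/3)². Power at 30 per arm uses the normal approximation Φ(d(1 − c/3)·√(30/2) − 1.96). For example, with d = 0.5 and c = 0.5: 0.4167 × 3.873 − 1.96 = −0.346, which gives 36.5%.

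| c | Contrast kept | Loss | Sample inflation | Power, d = 0.5 | Power, d = 0.8 |
|---|---|---|---|---|---|
| 0 | 100% | 0% | 1.00 | 49.1% | 87.3% |
| 0.1 | 96.7% | 3.3% | 1.07 | 46.5% | 85.0% |
| 0.25 | 91.7% | 8.3% | 1.19 | 42.7% | 81.1% |
| 0.5 | 83.3% | 16.7% | 1.44 | 36.5% | 73.3% |
| 1 | 66.7% | 33.3% | 2.25 | 25.2% | 54.2% |

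The Mann-Whitney test gives slightly lower figures: with an efficiency of 0.955, the 49.1% becomes 47.3%.

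**Step 4: leaving out the 20 piloted children.** This leaves 20 per arm. Power is 35.2% at d = 0.5 and 71.6% at d = 0.8. Exclusion therefore costs about as much as dilution at c = 0.5.

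**The case against.** The draw is random and equal, 10 per arm, so it creates no imbalance between the arms. The documents give no length for the focus group, and part of it is consultation. Against ten sessions of about 60 minutes, a pilot worth one session in ten (c = 0.1, itself an assumption) costs 3.3% of the contrast. The programme repeats and practises its skills in sessions 8 and 9, so earlier contact might add to the benefit rather than use it up. All of this stands. It makes the size of the loss uncertain and possibly nil, but it does not remove the conflict over the word untreated.

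A reader might infer three stronger things that the documents do not support:

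- **The contrast is certainly diluted.** It shrinks only if the pilot effect lasts and overlaps with the programme. The article shows neither.
- **The pilot precedes T1.** The article places the pilot before implementation and T1 just before IIG delivery. The order of the two can be guessed but is not stated.
- **Children answer T1 knowing their group.** The documents establish only that T1 follows allocation. When allocation is disclosed is a detail that a condensed article may leave to the full protocol.

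The plan does examine equivalence of the arms at T1, so the baseline is not ignored. A non-significant difference between two groups of 30 would not, however, rule out an expectation effect.

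**Conclusion.** The point holds as a contradiction together with an avoidable, conditional threat. The Method section exposes 10 of 30 wait-list children to programme content after randomisation, and the Programme evaluation section uses the whole arm as untreated from T1 to T2. The article states both, so this is not a matter of missing detail.

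The possible loss is c/3 of the T1–T2 contrast: zero at c = 0, about 3% to 17% for c between 0.1 and 0.5, and 33% as the upper bound. It rests on the assumption that the pilot effect lasts to T2 and overlaps with the programme. The power figures also rest on the assumed d and alpha, and they ignore any clustering within intervention groups.

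The position of T1 after allocation is a secondary weakness. It matters if children know their group when they complete the questionnaire, which the article does not say. The point is worth acting on because this is the trial's only controlled comparison, the article attributes its small sample to geography and logistics, and the remedy costs little.

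**What to change.** Complete T1 for all consenting children first, then randomise within school, with no piloting before T1. Draw the focus-group children from outside the randomised sample, for example from neighbouring grades at the two schools. The cost is a reordering of steps and pilot input from slightly older or younger children than the target group.

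If that is not feasible:

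- Keep the draw balanced across arms. Drawing from the IIG alone would spare the controls but give a third of one arm extra content and contact, replacing balanced exposure with one-sided exposure.
- Hold the pilot after T1, so that the baseline precedes exposure.
- Record focus-group membership and pre-specify a sensitivity analysis by it, for example the change-score comparison among the 20 unpiloted children per arm. Because the draw is random within each arm, this remains a randomised comparison. It has low power (35.2% at an assumed d of 0.5), so it should be read as an estimate beside the main result and not as a test.
- Reword the Programme evaluation section so that it no longer describes the whole DIG as untreated, and state where the focus group falls relative to T1.

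The fallback costs one recorded variable, one extra analysis and a change of wording.

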### Immediate intervention group (IIG)

All assenting children in the IIG will receive a 10–session CBT-based, group programme, each session will last approximately 60 minutes. The sessions will take place twice a week for five weeks. Groups consist of 8–10 participants. The programme will be delivered at schools during a time negotiated with the school. The Programme will start with activities that promote group cohesion and teamwork (session 1). In sessions 2 and 3 psycho-education, regarding emotions and thoughts, is given, and in session 4 bodily reactions to anxiety are addressed and relaxation exercises are introduced. Group participants are encouraged to practice these relaxation exercises throughout the duration of the programme. The next step (session 5) relates to recognising inner thoughts and the promotion of positive thinking. Session 6 introduces the concept of cognitive restructuring and introduces participants to problem solving skills. Self-evaluation and reinforcement is introduced in session 7. Sessions 8 and 9 allow for group participants to repeat and practice the new skills they have learnt, and session 10 covers relapse prevention and there is a party to celebrate the completion of the programme. At the start of the programme, parents or guardians and teachers will also be invited to attend an additional psycho-educational information session. This information session will provide an overview of the anxiety intervention programme, discuss the rationale underlying CBT-based programmes and explain the skills that children will be taught.

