### Delayed intervention group (DIG)

Participants in the DIG will be delivered the same intervention programme straight after the programme has been delivered to participants in the immediate intervention group, and they will also be asked to complete three questionnaires on four occasions, together with the children in the IIG.

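### The 3- and 6-month follow-up labels conflict with the stated timetable, which puts the two programme ends about 8 weeks closer together than the labels need

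*Protocol article*

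**What the plan says.** All places are in the protocol article.

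**Labels.** The Method section describes "3 month (T3 for IIG and T4 for DIG) or 6 month (T4 only for IIG) follow-up assessments". Programme evaluation uses the same labels for the maintenance comparisons. Data collection places the last assessment "six months after delivering the programme to the IIG, and three months after delivering the programme to the DIG (T4"). The fourth between-group hypothesis is framed at the three-month (DIG) and six-month (IIG) follow-ups.

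**Timetable.** For the length of the programme, the IIG section says "The sessions will take place twice a week for five weeks". Programme evaluation gives the same length for each arm: "Children in the IIG receive the anxiety intervention programme (5 weeks") and "Children in the DIG receive the anxiety intervention programme (5 weeks"). The DIG section says that this group "will be delivered the same intervention programme straight after the programme has been delivered to participants in the immediate intervention group". T3 is taken "Immediately after delivering the anxiety intervention programme to the DIG (T3"). The DIG and Programme evaluation sections have both groups assessed together on each of the four occasions, so T3 and T4 are each one shared date.

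**The concern.** The labels and the timetable cannot both be followed. If the DIG programme follows the IIG programme directly and lasts 5 weeks, an assessment made as it ends is not a 3-month follow-up of the IIG. A shared T4 cannot satisfy both of its stated intervals either.

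Maintenance of effect is one of the three things that Programme evaluation says the design can measure. If the timetable is followed and the labels are kept, a result about 5 weeks after the IIG programme would stand as 3-month maintenance. Depending on which T4 rule is obeyed, a result at about 4.1 months could stand as 6-month maintenance for the IIG. Both labels would overstate how long the effect had been observed. Under the other T4 rule, the DIG result would be labelled 3 months when it was obtained at about 4.9 months. Staff scheduling T4 from Data collection would have to break one of its two conditions.

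**Working it through.** **Inputs.** Programme length is 5 weeks per arm (IIG section; Programme evaluation). The DIG programme starts directly after the IIG programme (DIG section). T2 falls immediately after the IIG programme and T3 immediately after the DIG programme (Data collection). T4 is one joint assessment (Programme evaluation). Conversion: 1 month = 365.25 / 12 / 7 = 4.348 weeks, so 3 months = 13.04 weeks and 6 months = 26.09 weeks. The time taken by the T2 and T3 assessments themselves is treated as negligible.

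**1. What the labels imply.** Let *g* be the gap in weeks between the two programme ends.
- T3 is a 3-month follow-up of the IIG only if *g* = 13.04.
- T4 is at 6 months for the IIG and 3 months for the DIG only if *g* = 26.09 − 13.04 = 13.04 after rounding.

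The labels therefore agree with one another and require *g* to be about 13 weeks.

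**2. What the timetable gives.** With T1 at week 0:
- IIG programme: weeks 0 to 5, with T2 at week 5.
- DIG programme: weeks 5 to 10, with T3 at week 10.
- *g* = 10 − 5 = 5 weeks.

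The shortfall is 13.04 − 5 = 8.04 weeks.

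**3. T3 for the IIG.** 10 − 5 = 5 weeks, and 5 / 4.348 = 1.15 months, against a label of 3 months.

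**4. T4.**
- By the IIG rule: 5 + 26.09 = week 31.09.
- By the DIG rule: 10 + 13.04 = week 23.04.
- Difference: about 8.04 weeks.
- If the DIG rule is kept, the IIG is at 23.04 − 5 = 18.04 weeks = 4.15 months, not 6.
- If the IIG rule is kept, the DIG is at 31.09 − 10 = 21.09 weeks = 4.85 months, not 3.

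**5. Other ways of counting.** The table shows the difference between the two T4 dates when each interval is counted from programme end or programme start.

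| IIG counted from | DIG counted from | Difference (weeks) |
|---|---|---|
| end | end | 8.0 |
| start | start | 8.0 |
| start | end | 3.0 |
| end | start | 13.0 |

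None gives zero. Counted from the start of the IIG programme, T3 is at 10 / 4.348 = 2.3 months, still short of 3. Counting from the start also sits badly with Data collection, which times T4 from delivery of the programme.

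**The case against.** The strongest reply is that the labels are coherent and only one fact is missing. A break of about 8 weeks before or during DIG delivery, such as a school holiday, would make every label correct. The text leaves some room for this. The timetable is introduced as envisaged and no calendar dates are given. Groups hold 8–10 children, so 30 per arm means three or four groups (30/10 = 3; 30/8 = 3.75), across two schools and with one named delivery team. A condensed article may leave dates to the full protocol.

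Part of this stands. There is one defect, not two: the T3 and T4 conflicts are the same missing 8 weeks. A reader might infer that the labelled follow-ups are impossible in any event. The documents do not support that, because an undisclosed break would rescue them. As written, though, the article speaks against a break. One before the DIG programme contradicts "straight after the programme has been delivered to participants in the immediate intervention group" and the use of T2 as the DIG's immediate pre-programme measure. One within delivery contradicts the 5 weeks given for that step. This is stated text in conflict, not detail left out.

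Two further inferences are tempting and unsupported:
- **That follow-ups at unequal times will be pooled.** No section plans this. Programme evaluation sets out maintenance within each group and discloses that the DIG has no 6-month follow-up.
- **That the main comparison is compromised.** The randomised IIG–DIG contrast at T2 and the within-group tests (IIG T1 to T2, DIG T2 to T3) do not use the follow-up labels.

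**Conclusion.** The conflict is real and follows from the article's own statements. On the stated timetable, the IIG's T3 is about 5 weeks (1.15 months) after its programme, not 3 months. The joint T4 misses one of its two labels by about 8 weeks: it is either about 4.1 months after IIG or about 4.9 months after DIG.

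The effect is confined to the maintenance comparisons in Programme evaluation and the fourth hypothesis, where durability would be claimed at intervals that the timetable does not deliver. The conclusion assumes two 5-week deliveries back to back, intervals counted from programme end, and assessments of negligible length. A real but unstated gap of about 8 weeks between T2 and the DIG programme, or within its delivery, would make the labels right and the timetable text wrong. The sections would still need reconciling.

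**What to change.** Reconcile Method, the DIG section, Programme evaluation, the between-group hypotheses and Data collection by one of two routes. The delivery timetable itself is for the sponsor to settle.

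1. **If the stated timetable holds:** label every follow-up by actual weeks since that group's own programme end (T3 for the IIG at about 5 weeks; T4 at its true interval for each group). Say which T4 rule governs, and restate the 3- and 6-month maintenance claims and the fourth hypothesis to match. This costs wording only, and the stated follow-up becomes shorter where the labels overstate it.
2. **If a gap was intended:** state its length and position, and correct the wording that the DIG follows directly and the implied 5-week T2–T3 interval. That interval would become about 5 + 8 = 13 weeks for the DIG, against 5 weeks for the IIG's T1–T2. The text that treats these as like-for-like immediate pre-post periods should then acknowledge the difference.

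Splitting T4 into two dates about 8 weeks apart would not be enough. The IIG's T3 would still be at about 5 weeks under a 3-month label, and the joint assessment of both groups would be broken.
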